#### Data collection

The inclusion of patients will be conducted by oncologists at the first visit to the oncology department (see Fig. 2 for patient flow diagram). The study will be presented verbally to patients that meet the inclusion criteria. Patients will give their verbal consent to participate in the study, and if they agree to participate, the oncologist will contact the clinical research assistant to administer the baseline (T0) survey to the patients. The patients will be allowed to answer the questionnaire directly or to take it home and return it within a month to the research center. The T1 and T2 visits will be integrated into the patients’ clinical follow-up. The clinical research assistant will call a few days before the visit to the oncology department to remind them to plan for a further 20 min during their visit to fill in the questionnaire. Once again, if the patients wish, they will be allowed to take the questionnaire home and return it within a month to the research center. A reminder will be send after 2 weeks. Thirty patients will be contacted at T2 to participate in an interview on a voluntary basis (for phase 3), depending on their PA practice and characteristics.

The questionnaire will be filled in three times by the cancer patients: at diagnosis (T0), six months after diagnosis (T1) and one year (T2) after diagnosis. At each time, patients will respond to the questionnaire on physical activity, preferences and situational variables. At T0, patients will also provide information on medical, socio-economic and personality variables. At T2, patients will also provide information on personality variables, to address the stability of these characteristics among individuals facing such an important event as cancer.

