## Background

In France, the number of patients living with cancer has increased in the last decade, due to higher remission rates, as well as larger number of diagnosed cancers [1, 2]. The literature has demonstrated that physical activity (PA) can play an important role in decreasing patient mortality rates and in increasing patient well-being at different times during their cancer [3, 4]. In other words, PA is beneficial in primary, secondary and tertiary cancer prevention [5], and helps decrease the side effects of treatment [6]. Previous work has shown that cancer patients tend to decrease their PA from diagnosis to the initiation of treatment [7] and have difficulty in recovering their initial PA level after treatment [8]. Nevertheless, studies focusing only on a specific time in the cancer trajectory (before, during or after) [9] or using a single theoretical model [10] have limited our understanding of the determinants of PA practice and its interactions, as well as of PA trajectories before, during and after cancer.

Different individual factors have been identified as playing an important role in PA practice. For example, gender, age, education level, socio-professional category, ethnicity, or overweight seem to impact PA levels in the general population [11] and among cancer patients [12]. Variables relating to personal disposition (traits), such as hope or optimism, have positive consequences on cancer [13–15], as they encourage the use of coping strategies, especially with regard to motivation [16], passion [17], and emotional regulation [18]. Moreover, physical activity prescription and social support from medical and paramedical staff seem to impact PA practice [19, 20]. While these variables appear to have an effect on PA practice, they are specific to individuals and to their direct environment, and their interactions have not often been analyzed [21].

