### Study aims

The aim of this mixed-method study is to identify the variables of the socio-ecological model facilitating PA practice, as well as PA levels and preferences (see Fig. 1) at different times during the course of cancer (at diagnosis, during treatment, after treatment). The results from the present work will help to identify key levers of PA practice and their interactions among cancer patients, from diagnosis to remission, in a socio-ecological approach.

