#### Scales

The questionnaire will include four main sections and different scales: medical and socio-economic variables, personality traits, situational variables and physical activity. The scales will be chosen on the basis of their validation in French and their suitability to PA and cancer patients, when available.

Medical data will be completed by the clinical research assistant, and will include: patient care plan, actual patient trajectory (treatment completion, frequency, type), symptoms and complementary treatment (fatigue, pain, nutrition).

Sociological variables will include age, gender, education, socio-professional category, professional activity, marital and socio-economic status, and place of residence. An 11-item scale to evaluate precariousness and health inequality (EPICES scores, [37]) will explore all the dimensions of precariousness. Life habits (tobacco, alcohol, substance use) and PA practice before diagnosis will help to identify inter-determinant relationships. Medical data (co-morbidities, fatigue, sleep, pain) will also be collected from patients’ perspective.

Personality traits will be approached via two validated scales: Trait Hope [38] and Trait Optimism [39]. Trait Hope will be assessed using the Dispositional Hope Scale [40], validated in French [38]. The Trait Hope Scale contains four “agency” items, four “pathway” items, and four “filler” items. Respondents will be asked to rate the items on an 8-point Likert scale ranging from 1 “definitely false” to 8 “definitely true”. The Life Orientation Test-Revised (LOT-R, [39]), comprises six items and four fillers, and will be rated on a 5-point Likert scale, ranging from 1 “strongly disagree” to 5 “strongly agree”.

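### The diagnosis questionnaire (T0) may go home for up to a month with no tie to treatment start, so answers given on treatment can be analysed as baseline

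*Protocol article*

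**What the plan says.** All places are in the protocol article.

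- **When T0 is handed out** (Phase 2, Data collection): "The inclusion of patients will be conducted by oncologists at the first visit to the oncology department". The clinical research assistant then administers the baseline survey.
- **When T0 comes back** (same section): patients are "allowed to answer the questionnaire directly or to take it home and return it within a month to the research center". The same option applies at T1 and T2. The text adds "A reminder will be send after 2 weeks"; in sequence this follows the T1 and T2 arrangements, and it does not refer to treatment.
- **What T0 stands for** (same section): the three administrations are "at diagnosis (T0), six months after diagnosis (T1) and one year (T2) after diagnosis".
- **What the study must tell apart** (Study aims): physical activity (PA) "at different times during the course of cancer (at diagnosis, during treatment, after treatment".
- **Link to treatment** (Eligibility criteria): patients must have been sent to an oncologist before any cancer treatment started. This governs entry, not when the form is filled in.
- **Related data** (Scales): the research assistant records "patient care plan, actual patient trajectory (treatment completion, frequency, type". Separately, "PA practice before diagnosis will help to identify inter-determinant relationships".
- **Use of T0** (Data analysis): PA profiles and trajectories are identified by latent class growth analysis, and relations among variables by multilevel structural equation modeling.

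**The concern.** The entry rule makes T0 look like a pre-treatment measurement, but the return rule does not keep it one. A patient can be included before treatment, take the form home, begin treatment, complete the form and return it on time. That form is then labelled as a diagnosis value.

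The article itself expects PA to be unstable around this point: the Background says that "cancer patients tend to decrease their PA from diagnosis to the initiation of treatment". Strictly, that sentence covers change up to the start of treatment, so it bears on any delayed form, including one completed before treatment.

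What is at stake is the first of only three points on each trajectory. The latent class analysis rests on those points, and the trajectories help to select the Phase 3 interviewees. The situational scales (anxiety, depression, state hope, motivation and others) are in the same questionnaire, so outcome and predictors would be mistimed together. If completion dates are not kept, mistimed forms cannot be reliably identified afterwards.

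**Working it through.** The plan gives no figure on this point to reproduce. The check is mainly a reading of the text, followed by illustrations.

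**Step 1. Can a compliant form be completed on treatment?** Entry must precede treatment. The form is due back within one month of being given out. No stated rule places first treatment more than a month after inclusion, and none places completion before first treatment. So a form completed on treatment is compatible with every stated rule.

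**Step 2. Does other stated information prevent this?** The treatment trajectory is recorded, but the items named are completion, frequency and type, and no use of them to define or restrict T0 is described. PA before diagnosis is collected as a separate variable, not as the T0 measure. Both could help in interpretation; neither protects T0.

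**Step 3. Can the extent be calculated?** No. It needs the time from inclusion to first treatment and the take-home share. Neither is given. It also depends on the period that the PA items ask about, which the article does not state.

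**Step 4. Illustration of the T0 level.** Let p0 be true compliance before treatment, f the share of T0 forms completed on treatment, and r the relative drop in compliance by then. Observed T0 = p0 × (1 − f × r). Take p0 = 15%, the rate cited for an earlier breast cancer cohort under Sample size and sampling method. The article does not call it a pre-treatment rate, so its use here is an assumption, as are f and r.

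- f = 10%, r = 25%: 0.15 × (1 − 0.025) = 14.6%
- f = 25%, r = 50%: 0.15 × (1 − 0.125) = 13.1%
- f = 50%, r = 50%: 0.15 × (1 − 0.25) = 11.3%

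**Step 5. Illustration of the T0-to-T1 change.** Assume 30% of T0 forms are completed on treatment and p0 = 15%.

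- *T1 is 7.5% and late T0 forms are already at 7.5%.* Observed T0 = 0.7 × 15 + 0.3 × 7.5 = 12.75%. The fall appears as 12.75 − 7.5 = 5.25 points instead of 7.5, which is 30% smaller.
- *T1 is 7.5% but late T0 forms are only halfway, at 11.25%.* Observed T0 = 10.5 + 3.375 = 13.875%. The fall appears as 6.375 points, which is 15% smaller.
- *Late T0 forms are at 7.5% but compliance has recovered to 15% by T1.* Observed T0 = 12.75%. A true change of zero appears as a rise of 2.25 points.

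Both the size and the form of the error therefore depend on inputs that the article does not give.

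**Step 6. Is zero mixing plausible?** If each of the 693 planned patients independently had a 1% chance (assumed) of completing T0 after treatment start, the chance that none did would be 0.99^693, about 0.1%. Under that assumption some mixing is very likely, but this says nothing about how much.

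**The case against.** The strongest reply has four parts.

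- **The month limits return, not completion.** A form may be filled in the same evening and posted later, and take-home is only an option. This is right, and it rules out reading the month as a completion delay. It does not close the gap, because without a completion date early and late forms look the same.
- **Date fields and rules for late forms belong in the case report form or the SAP.** Their absence from an article is indeed no finding. The point rests on something the article does state: a one-month take-home window for a time point that it labels as diagnosis.
- **Partial safeguards exist.** The treatment trajectory and PA before diagnosis are collected. They help, but the article uses neither to define T0.
- **Discarding late forms could be costly.** If 10% to 40% of forms were late (assumed), 69 to 277 of 693 patients would lose a baseline, against an allowance of 5% for loss, or 33 patients (693 − 660). These would tend to be the patients treated soonest. This stands, and it is why late forms should be kept and analysed at their actual time.

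A reader might go further and infer that T0 certainly will be mixed, that the early fall in PA is shrunk by some 10% to 40%, or that the comparisons between hospitals and cancer localizations are biased. The article supports none of these. The 10% to 40% merely returns an assumed share of late forms, and does so only if patients just starting treatment already have their six-month compliance. No figures on treatment delay by hospital or localization are given. The Data analysis section names no change score, and does not say that the group comparisons use T0.

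**Conclusion.** The point holds as a weakness in a stated rule. Followed exactly, the plan allows T0 forms to be completed after treatment has begun and analysed as diagnosis values, which blurs a distinction that the aims require. That T0 is meant to be pre-treatment is inferred from the entry criterion and the aims; the article does not use the word.

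The extent and direction of the error in PA trajectories and situational scores are unknown, and every percentage shown above for T0 or for the change is illustrative. The conclusion rests on the article alone; a full protocol or SAP may already contain a completion rule. This is a cheap improvement worth making, not a flaw that invalidates the study.

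**What to change.** - Make completion at the inclusion visit the default for T0.
- If the form goes home, ask for completion as soon as possible and before first treatment. Both parts matter: the second protects the pre-treatment status, and the first limits the drift in PA that the Background describes before treatment.
- Record the completion date of the form and the date of first treatment.
- Keep forms completed after treatment start. Analyse them at their actual time, not as pre-treatment baseline, and add a sensitivity analysis that excludes them.

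The cost is two date fields, a changed instruction, and some patients without a pre-treatment T0. Their number depends on how often forms are late, which the recorded dates would show. The change concerns measurement only and leaves treatment scheduling untouched.

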#### Sample size and sampling method

The principal judgment criterion is the compliance with PA recommendations (i.e. 150 min of at least moderate PA per week). In a previous cohort study [36], 15% of breast cancer patients (*n* = 466) managed to comply with these recommendations. Considering the fact that patients with factors facilitating PA practice are twice as likely to comply with these recommendations (Odds Ratio = 2), with an alpha risk of 5% and a power of 80%, 660 cancer patients will be included (220 per cancer localization). Taking into account a potential loss of 5% of the patients (11 patients per localization), we hope to include and follow a total of 693 patients (231 for each cancer localization). The data collection will last 12 months, reaching 30 patient inclusions per month in each hospital.

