#### Data analysis

The analyses will be performed using SPSS and SAS software. Basic descriptive statistics, including means, standard deviations and frequencies will be calculated. A comparison of PA levels will be made across groups of patients depending on their hospital site and cancer localization. An identification of PA profiles and trajectories during the study will be conducted using a latent class growth analysis [47]. Relationships between the individual and interpersonal variables of the socio-ecological model will be tested using multilevel structural equation modeling. Profiles of PA practice among cancer patients will also be approached through the qualitative data collection, to identify further societal and policy factors, using Nvivo software.

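### Waves at 0, 6 and 12 months alias season with the T1 contrast within each patient, so individual six-month changes and profiles can carry season of inclusion unless calendar date is modelled

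*Protocol article*

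**What the plan says.** The Phase 2 Data collection section of the protocol article sets the questionnaire "at diagnosis (T0), six months after diagnosis (T1) and one year (T2) after diagnosis". Patients may complete it at the visit or "take it home and return it within a month to the research center". The Scales section says that PA is self-reported and covers work, mobility and leisure.

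The Sample size section gives the accrual: "The data collection will last 12 months, reaching 30 patient inclusions per month in each hospital", for a target of 693 patients in equal numbers per cancer localization.

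The Phase 2 Data analysis section compares PA levels by hospital and localization, and states: "An identification of PA profiles and trajectories during the study will be conducted using a latent class growth analysis [47]". It also plans multilevel structural equation modelling. According to the Abstract, the thirty Phase 3 patients are identified from their PA profiles six months after inclusion, when only T0 and T1 exist. The article does not mention season or calendar month.

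**The concern.** The spacing of the waves is half a year. A patient included in the active season is measured active, inactive, active; a patient included in the inactive season is measured in the reverse order. Leisure activity and active travel plausibly vary with season in north-east France. For a single patient, a seasonal dip or peak at T1 then looks the same as a disease- or treatment-related one.

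The whole-cohort mean is largely protected because entry is staggered over the year. What is exposed is anything built on individual change around T1: the growth trajectories, a six-month profile resting on T0 and T1 alone, and the Phase 3 selection based on it. If one localization fills its quota much faster than another, their mean six-month changes could also differ because of season.

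**Working it through.** **Inputs.** From the documents: waves at 0, 6 and 12 months; 693 patients; 30 inclusions per month in each of two hospitals. Assumed, because the documents give no figure: a sinusoidal seasonal term of amplitude A = 0.1, 0.2 or 0.3 on the log scale of weekly PA, a within-patient SD σ of 0.4, 0.6 or 1.0 per wave, and no true change over time.

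**1. The plan's accrual figure.** 693 / (2 × 30) = 11.55 months, which agrees with the stated 12 months (12 × 60 = 720 places). T0 therefore falls in every season across the cohort.

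**2. Aliasing within a patient.** Let season be s(t) = A·cos(2π(t − φ)/12). Then s(t+12) = s(t) and s(t+6) = −s(t), so:
- T2 − T0: the seasonal part is 0.
- T1 − (T0+T2)/2: the seasonal part is −2A·cos(2π(t₀ − φ)/12), anywhere from −2A to +2A.
- T1 − T0: the same −2A to +2A.

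At A = 0.2 the extreme is 0.4 log units: exp(−0.4) = 0.67, so T1 is about one third lower from season alone.

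**3. Cohort mean.** Averaging the contrast in step 2 over even inclusion, at the worst phase φ:

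| Length of inclusion | Largest mean contrast |
|---|---|
| 3 months | 1.80A |
| 6 months | 1.27A |
| 9 months | 0.60A |
| 11 months | 0.18A |
| 11.55 months | 0.08A |
| 12 months | 0 |

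The planned accrual leaves at most 0.08A. A localization whose quota filled in six months could carry 1.27A; at A = 0.2 that is 0.25 log units, and exp(−0.25) = 0.78.

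**4. Individual contrasts.** Over a full year of even inclusion the seasonal variance of T1 − (T0+T2)/2 is 4A² × ½ = 2A², and the residual variance is σ²(1 + ¼ + ¼) = 1.5σ². Season's share is 2A² / (2A² + 1.5σ²):

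| A | σ = 0.4 | σ = 0.6 | σ = 1.0 |
|---|---|---|---|
| 0.1 | 7.7% | 3.6% | 1.3% |
| 0.2 | 25.0% | 12.9% | 5.1% |
| 0.3 | 42.9% | 25.0% | 10.7% |

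Simulation with 11.55 months of inclusion gives values up to one percentage point lower, hence about 1% to 42%. For T1 − T0 alone the residual variance is 2σ², so the share is A² / (A² + σ²): at A = 0.2, 20%, 10% and 4% for σ = 0.4, 0.6 and 1.0.

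**5. Selection on a six-month change.** In the same simulation (A = 0.2, σ = 0.4 to 0.6, no true change, seasonal peak at the start of inclusion), 66–74% of the quarter with the steepest T0-to-T1 decline had been included in the high-PA half-year. The corresponding share was 22–30% in the quarter with the largest increase and 48% in the cohort.

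**6. Latent classes.** Latent class growth models were fitted to 693 simulated patients with no true trajectory, and the number of classes was chosen by BIC. A class counted as V-shaped if its dip or peak at T1 exceeded 0.4.
- Between-patient log-SD 1.0, σ = 0.4 or 0.6: the share of patients in such classes was 0.2% or 0% at A = 0.1, 0% or 0.2% at A = 0.2, and 4.5% or 0% at A = 0.3, against 0% or 0.8% with no season.
- Standardized scale, between-patient and residual SD both 0.7: 0% at A = 0.1 and 0.2, 0.1% at 0.3, and 26% at 0.5.

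Classes form mainly on stable PA level, so marked seasonal classes need a large amplitude.

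**The case against.** The strongest reply has four parts.

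- **The schedule is sound.** Waves half a year apart are not an error, T2 − T0 is free of season, and inclusion over a year balances the mean. All of this stands.
- **Season would mostly be noise.** Nothing in the article links season of inclusion to personality traits, education or precariousness. If they are independent, season blurs individual change without confounding the determinants. This also stands; bias in the study's objectives on PA evolution and its determinants is not shown.
- **The sizes are assumed.** No amplitude or SD comes from the documents, and real variation in response to treatment would shrink season's share. This stands, and it is why the result is a wide range.
- **Covariates belong in the analysis plan.** The article lists none for any model, so the absence of season shows little. This stands as far as omission goes. The aliasing itself, however, comes from the schedule that the article fixes, and the calendar information has to be kept for the analysis to use it.

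A reader might infer more: that season reproduces a decline and recovery that will be taken for a cancer trajectory. The documents do not support this. About half of the patients (48–52%) would show the dip and the rest the reverse, and the Background describes a decrease followed by difficult recovery, not a symmetric V. Nor can season produce a sustained increase, because T0 and T2 share a season.

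**Conclusion.** The concern holds in a limited form. Within each patient, season is fully aliased with the T1 contrast; this follows from the wave times and is certain, given any seasonal swing that is opposite in sign half a year apart. The cohort mean is nearly clean (at most 0.08A with even inclusion over 11.55 months) and T2 − T0 is unaffected.

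Exposed are individual T0-to-T1 changes, the six-month profiles behind Phase 3 selection and, only if quotas fill at different speeds, the localization comparison. The size cannot be determined from the documents. Under the stated assumptions season accounts for about 1% to 42% of the variance in individual T1 contrasts, while spurious V-shaped classes stay at about 0–5% of patients for A up to 0.3. This is a worthwhile improvement to the analysis and not a fault in the schedule.

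**What to change.** - Use the completion date of each questionnaire, not only the visit date, since a form may come back up to a month later.
- Add season as a time-varying covariate of PA (sine and cosine of calendar date) in the latent class growth analysis and the structural equation model. Staggered entry separates calendar date from wave across patients, so the terms can be estimated.
- Adjust the hospital and localization comparisons for the same terms.
- Tabulate class membership and the Phase 3 selection by month of inclusion as a check.

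The cost is a completion date on each form, two model terms and a descriptive table. No extra patients, visits or change to the waves are needed.

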**Methods/design:**

A nested sequential mixed-method design QUAN (QUAL+QUAL) will be used, with qualitative studies embedded in the quantitative study to broaden our understanding of the determinants of PA practice. The design is sequential, since qualitative data on medical staff will be collected before patient inclusion (Phase 1), followed by quantitative patient data collection lasting one year (Phase 2) and a final qualitative data collection one year after inclusion (Phase 3). Phase 1 will be a case study in the two hospitals involved in the study, exploring knowledge of and support for PA practice among medical staff. Through interviews and documental analyses, the PA support dynamic will be evaluated with regard to PA prescription. Phase 2 will be a one-year observational study among 693 cancer patients. Quantitative medical, social, dispositional and psychological data, PA practices and preferences, will be collected at diagnosis, and six months and one year thereafter. Phase 3 will be a retrospective study, evaluating societal and policy factors, as well as unexpected factors playing a role in PA levels and preferences among cancer patients. For this phase thirty patients will be identified six months after inclusion on the basis of their PA profiles. Quantitative data will provide the main dataset, whilst qualitative data will complete the picture, enabling determinants of PA practice and their interactions to be captured throughout the cancer trajectory.

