**Fig. 1 Fig1:**
[figure not shown]
Socio-ecological model used in present protocol

The specific objectives are:to evaluate the evolution of PA practices (level, context, preferences) from diagnosis to remission;to understand the interactions and reciprocal effects between sociological, dispositional, psychological and situational variables and PA level, and their evolution from diagnosis to remission;to analyze how policies and the social environment (medical staff) promote PA practice among cancer patient, crossing individual and interpersonal variables.

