Situational variables will include passion [41], satisfaction of basic needs in sport [42], state-hope [38], self-determined motivation for PA [43], anxiety and depression [44]. The two dimensions of passion (harmonious and obsessive) will be measured on a 12-item scale [41], where answers will be rated on a 7-point Likert, ranging from 1 “totally disagree” to 7 “totally agree”. The basic needs satisfaction (autonomy, competence and relatedness) will be collected using a validated French scale in the sports context [42]. Participants will answer on a 7-point Likert scale, ranging from 1 “totally wrong” to 7 “totally true”. The Adult dispositional Hope scale [38] will be used to explore state-hope. This scale includes 6 items (2 dimensions: operational and motivational components), and will be answered on a 6-point Likert scale, ranging from 1 “totally disagree” to 6 “totally agree”. All six dimensions of self-determined motivation for PA [43] will be explored using an 18-item scale, with a 6-point Likert response scale ranging from 1 “does not correspond at all” to 6 “corresponds totally”. The Health Anxiety Depression Scale, adapted into French [44] will measure anxiety (7 items) and depression (7 items), on a three-point scale.

Physical activity and sedentary behaviors will be measured using the self-reported Global Physical Activity questionnaire [45]. This questionnaire will measure the frequency, intensity, and duration of PA practice, as well as its context (work, mobility or leisure). PA preferences will also be evaluated in terms of type of practice, duration, intensity etc. [46].

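### Changeable social variables are asked only at diagnosis, so their reciprocal effects with physical activity cannot be estimated, and the abstract misstates the schedule

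*Protocol article*

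**What the plan says.** The operative timetable is in Phase 2, Data collection. At all three visits (T0 at diagnosis, T1 at six months, T2 at one year), "At each time, patients will respond to the questionnaire on physical activity, preferences and situational variables". Then "At T0, patients will also provide information on medical, socio-economic and personality variables". One block returns at the end: "At T2, patients will also provide information on personality variables, to address the stability of these characteristics".

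The Scales section defines the social block: "Sociological variables will include age, gender, education, socio-professional category, professional activity, marital and socio-economic status, and place of residence". It describes the 11-item EPICES precariousness score alongside these. The situational variables listed there are psychological scales only. The PA questionnaire, given at each visit, records frequency, intensity and duration "as well as its context (work, mobility or leisure").

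Two other places describe something wider. The abstract (Methods/design) says: "Quantitative medical, social, dispositional and psychological data, PA practices and preferences, will be collected at diagnosis, and six months and one year thereafter". The second specific objective under Study aims is to understand "interactions and reciprocal effects between sociological, dispositional, psychological and situational variables and PA level", together with how these evolve up to remission.

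**The concern.** The timetable gives social variables one measurement, the abstract gives them three, and the second objective needs more than one if effects are to run in both directions. Age and gender raise no difficulty, and education rarely does. Professional activity, marital status and socio-economic status can all change in the year after a cancer diagnosis.

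The choice is made at data collection. An analysis plan can choose the model, but it cannot supply a status that nobody asked about at T1 or T2.

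Work deserves particular attention because it bears on the main endpoint. The sample size section says: "The principal judgment criterion is the compliance with PA recommendations (i.e. 150 min of at least moderate PA per week"). It excludes no context, so minutes of activity at work may count towards compliance. A model of PA at T1 or T2 would have current motivation, anxiety and depression available, but work status only as it stood at diagnosis.

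**Working it through.** The plan gives no figure to reproduce here. The check sets the timetable beside the abstract and then counts the paths that the timetable allows.

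**Step 1: which block is asked when (Data collection), against the abstract.**

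| Block | T0 | T1 | T2 | Abstract |
|---|---|---|---|---|
| PA and preferences | yes | yes | yes | all three |
| Situational scales (psychological) | yes | yes | yes | all three |
| Personality | yes | no | yes | all three |
| Socio-economic | yes | no | no | all three |

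The abstract overstates the social block by two visits and the personality block by one.

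**Step 2: does another source carry social status forward?** The situational list in Scales contains no social or employment item. The medical data completed by the research assistant cover care plan, treatment trajectory, symptoms and complementary treatment, with no work status. Phase 3 gives a retrospective qualitative account for 30 patients. None of these supplies social status at T1 or T2 for the cohort.

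**Step 3: count the paths.** Let X be a changeable social variable. With X and PA both measured at T0, T1 and T2, there are four cross-lagged paths between adjacent visits:

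- social to PA: X0 → PA1 and X1 → PA2;
- PA to social: PA0 → X1 and PA1 → X2.

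Under the timetable only X0 exists.

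- X0 → PA1 is estimable, as is the longer-lag X0 → PA2. X1 → PA2 is not.
- PA0 → X1 and PA1 → X2 are not estimable: 0 of 2.
- One of the four adjacent-visit paths remains, and change in X cannot be described.

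PA before diagnosis, also collected according to Scales, could be related to X0. That path is weak: the PA is recalled, and social status before diagnosis is not available for adjustment.

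**Step 4: the work items.** Work, mobility and leisure PA are each measured at T0, T1 and T2, so a fall in work minutes from T0 to T1 is seen directly. Three things stay unknown:

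- whether the patient stopped work or continued on lighter duties;
- whether any lost mobility minutes were commuting;
- current work status, as a covariate in a model of PA at T1 or T2.

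**The case against.** **Objective 2 is a collective phrase.** It lists four families of variables together, and since the sociological family includes age and gender, it cannot mean a path from PA to every item. Reciprocal effects are estimable for the situational scales, and treating social variables as baseline determinants or moderators is a coherent design. The expected result in Table 1, a model of interaction over time between social and psychological variables, can be met in that form. This stands, and it lowers the weight of the point. It does not remove it: the objective names sociological variables without restriction and adds their evolution, which the changeable ones cannot show on one measurement.

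**The abstract is only a loose summary.** The detailed timetable is clear enough that staff would not be misled. That is fair, but the sentence is still wrong as written.

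**The T0-only reading rests on omission in a condensed article.** Medical data show that the timetable is not a complete data list, since treatment completion must be recorded after T0. This lowers certainty a little. The timetable nevertheless states what is asked each time and names the single block repeated at T2, so the reading is firm for the patient questionnaire. For EPICES it is an inference.

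**Stronger readings a reader might reach.** One is that patients who leave work will lose compliance and that the model will then blame motivation or anxiety. The documents do not support this. Work minutes are observed at T0 and afterwards, so an analyst can split the change by context or analyse non-work PA. A patient in a sedentary job has no work minutes to lose. Nor do the documents say that stopping work lowers total PA.

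Another is that using T0 work status shrinks an odds ratio and costs a calculable amount of power. That would require an assumed share of patients leaving work, an assumed share working at diagnosis, and the sample size section's odds ratio of 2, which refers to unspecified facilitating factors and not to employment. Such figures would illustrate the assumptions and would say nothing about this study. The effect of baseline status is also a legitimate quantity in itself, not a biased version of the other.

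**Conclusion.** The point holds, with low to moderate weight. The abstract contradicts the timetable for social data and, to a lesser degree, for personality. For changeable sociological variables, the reciprocal and evolution parts of the second objective cannot be estimated: 0 of 2 PA-to-social paths, and no within-patient change. Baseline social effects on later PA, and their moderation, remain estimable.

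For work, the gap is narrow but real: lost work minutes are visible, while the reason for the loss and current work status are not.

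The conclusion rests on taking the Data collection section as the full list of what patients are asked at each visit. It needs no assumption about how many patients change status, and it makes no claim about the size or direction of any bias.

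**What to change.** 1. Ask current professional activity at T1 and T2 and, if wanted, marital status. Word the work question so that stopping work or sick leave can be told from continuing on changed duties. Enter it as a time-varying covariate in the structural equation model; if the reciprocal path is wanted, it must also be modelled as an outcome.
2. Correct the abstract to the actual timetable: PA, preferences and situational scales at three visits; personality at T0 and T2; socio-economic data at T0, plus any item repeated under step 1.
3. Restrict the second objective so that sociological variables not repeated are baseline predictors or moderators only, with no claim of reciprocal effects or change.

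The cost is one or two short questions per follow-up visit, within a questionnaire for which patients are asked to allow 20 minutes, and a small amendment. Steps 2 and 3 change wording only. If the sponsor declines step 1, they still remove the contradiction, though the social data remain baseline only. Repeating EPICES is a separate burden trade-off that the sponsor may reasonably decline; it is not part of this fix.
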